## Abstract

**Background:**

Emotional disorders are common, and they have become more prevalent since the COVID-19 pandemic. Due to a high attendance burden at the specialized level, most emotional disorders in Spain are treated in primary care, where they are usually misdiagnosed and treated using psychotropic drugs. This contributes to perpetuate their illness and increase health care costs. Following the IAPT programme and the transdiagnostic approach, the PsicAP project developed a brief group transdiagnostic cognitive-behavioural therapy (tCBT) as a cost-effective alternative. However, it is not suitable for everyone; in some cases, one-on-one sessions may be more effective. The objective of the present study is to compare, in cost-benefit terms, group and individual tCBT with the treatment usually administered in Spanish primary care (TAU).

**Methods:**

A randomized, controlled, multicentre, and single-blinded trial will be performed. Adults with mild to moderate emotional disorders will be recruited and placed in one of three arms: group tCBT, individual tCBT, or TAU. Medical data and outcomes regarding emotional symptoms, disability, quality of life, and emotion regulation biases will be collected at baseline, immediately after treatment, and 6 and 12 months later. The data will be used to calculate incremental cost-effectiveness and cost-utility ratios.

**Discussion:**

This trial aims to contribute to clinical practice research. The involvement of psychologists in primary care and the implementation of a stepped-care model for mental disorders are recommended. Group therapy and a transdiagnostic approach may help optimize health system resources and unblock waiting lists so that people can spend less time experiencing mental health problems.

**Trial registration:**

ClinicalTrials.gov: NCT04847310; Protocols.io: bx2npqde. (April 19, 2021)

**Supplementary Information:**

The online version contains supplementary material available at 10.1186/s12888-022-03726-4.

## Background

Depressive, anxiety, and somatoform disorders are the most common mental health problems in the world [1, 2]. In 2019, the global prevalence of depressive disorders was 3.76 and 4.05% for anxiety disorders; Europe had the highest prevalence of the former (4.37%) and the second-highest of the latter (5.15%) [3]. The prevalence of both depressive (6.04%) and anxiety disorders (5.42%) in Spain is even higher; depression has continued to increase over the past few years to the point where the country has the third-highest prevalence after Greenland and Greece [3]. All these mental conditions have worsened during the COVID-19 pandemic [4, 5].

In Spain, mental health care is integrated in the national health system (at the specialized care level). It is free and unlimited because it is funded through public taxation. However, as in many other countries, users must have previously accessed primary care first. This is organized in territorially delimited community centres that employ multidisciplinary teams of general practitioners (GPs), nurses, and social workers but few psychologists (though some have been incorporated recently). Since specialized care waiting times are too long, many mental health cases are treated in primary care by GPs, who have consultations of less than 10 min and insufficient training in psychology to handle them [6]. This leads to misdiagnosis [7–9] and poor treatment (or even non-treatment) [6, 10], medication being the principal recourse. Spain is the eighth highest consumer of antidepressants of any OECD country, with 77 defined daily doses (DDDs) per 1000 habitants, which is double the OECD average [11]; and since 2010, anxiolytic and hypnotic use has increased by 200%, reaching in 91 DDDs in 2020 [12]. The use of psychotropic drugs as a first-line treatment may contribute to relapse and the duration of emotional disorders (EDs) [13] that generate large personal, social, and economic costs [14, 15]. Psychotherapy is the treatment of choice for common mental disorders due to its non-invasive nature [16]; patients tend to prefer psychological treatment, and though its short-term effects may be similar to those of pharmacotherapy, they can be more enduring [17–19]. Moreover, psychotherapy can save costs since it can be abbreviated when the patient or the context requires it, as happens in primary care [20].

According to Chisholm et al. [10], an increase in investment in care for depression and anxiety disorders would achieve very positive, long-term, cost-benefit ratios, substantially reducing the number of cases and increasing the number of healthy life-years. Some countries have begun to implement evidence-based psychological therapies in primary care settings. The Improving Access to Psychological Therapies (IAPT) programme [21] started in the UK in 2008. It provides community stepped-care low/high-intensity psychological treatment recommended by the National Institute for Health and Care Excellence (NICE) for EDs; cognitive-behavioural therapy (CBT) is the most widely used [16]. Through empirically-supported treatment and session-by-session monitoring, the IAPT programme has achieved great clinical and functional recovery rates with moderate to large effect sizes [21, 22]. It is now being replicated in other countries [23–25].

However, the IAPT programme has several limitations [21]. For example, whereas comorbidity is the most common clinical situation, its assessment and treatment processes are guided by categorical diagnoses, and this may affect therapy outcomes [26, 27]. Furthermore, some authors have observed that certain EDs improve with treatments that do not address them specifically [27]. As a result, a transdiagnostic approach has been developed that focuses on the dysfunctional emotion regulation strategies and cognitive processes that various mental disorders have in common [28–30]. In recent years, this approach has proven to be effective for reducing emotional symptoms and improving quality of life [31–33]. Moreover, transdiagnostic approaches might further reduce costs, as different conditions can be targeted in single group sessions.

Recently, the large national PsicAP study [34, 35] showed the effectiveness of a brief, group, transdiagnostic CBT compared with the treatment usually provided in Spanish primary care, achieving medium effect sizes in the reduction of emotional symptoms and recovery rates that were similar to those obtained by the IAPT programme. A recent trial by Corpas et al. [36] also obtained medium to high effect sizes for symptoms in the group intervention and very high effect sizes in the improvement of emotion regulation strategies and cognitive biases. However, some authors suggest that individual therapy may be more effective than group therapy, especially in the short-term [31, 37]. Some people prefer the former due to the fear of self-disclosure or the anxiety of social interaction [38]. In addition, the individual format also allows the therapist to establish a better relationship with the patient, which can benefit clinical outcomes [39]. The PsiBrief project [40, 41] compared brief versions of individual and group transdiagnostic CBT with the usual treatment in Spanish primary care. The results did not show any difference between the psychotherapy clusters in reducing emotional symptoms, though they were both more effective than primary care treatment (with moderate effect sizes). Unfortunately, the project did not report on patients’ treatment satisfaction or preference, and it is recommended that this should be considered when choosing the therapy [16]. Furthermore, as far as we know, few studies have included cost-benefit analyses of psychological treatments in primary care and even fewer transdiagnostic approaches.

### Objectives and hypotheses

We believe that the implementation of transdiagnostic therapy at the primary level using a stepped-care model would save costs and reduce waiting lists. Mild to moderate cases could be treated in primary care and severe ones could be referred to specialized care for combined and more intensive therapies.

The proposed trial aims to compare, in terms of cost-effectiveness and cost-utility, a brief, transdiagnostic CBT in two different formats, individual and group, with the treatment ordinarily administered in primary care (treatment as usual [TAU]) for mild to moderate EDs (i.e., depressive, anxiety, and somatoform disorders). We expect that:

#### Hypothesis 1

Individual treatment will be generally as effective as group treatment in reducing emotional symptoms and cognitive-emotional regulation biases (i.e., both will show similar post-intervention size effects).

#### Hypothesis 2

The TAU will be the least effective (i.e., with significantly lower post-intervention size effects).

#### Hypothesis 3

The group therapy will return the best results in terms of cost-effectiveness and cost-utility.

#### Hypothesis 4

The TAU will have the least cost-effectiveness and cost-utility ratios.

#### Hypothesis 5

The same results will be found across the follow-up assessments (6 and 12 months after intervention).

## Methods

This protocol has been registered at ClinicalTrials.gov (NCT04847310) and Protocols.io (bx2npqde) and follows the SPIRIT statement [42].

### Trial design

This intervention trial has a randomized, controlled, multicentre, and single-blinded design with 3 parallel groups, a 1:1:1 allocation ratio, and 4 measurement times: pre-intervention, immediately after the intervention, and two follow-ups (at 6 and 12 months; see Fig. 1).

**Fig. 1 Fig1:**
[figure not shown]
Study design flowchart. TAU: treatment as usual; tCBT: brief transdiagnostic cognitive-behavioural therapy

### Study settings

The RCT will be performed in two primary care centres and one mental health unit in the province of Cordoba (region of Andalusia, Spain): the Carlos Castilla del Pino Health Centre, the Levante Sur [name] Solís Health Centre, and the Community Mental Health Unit of Montilla.

### Eligibility criteria

Participants will be adult (18–65-year-old) men and women with mild to moderate EDs (i.e., depressive, anxiety, and/or somatoform disorders) according to the measurement tools (see Data Collection). People over 65 will be excluded to prevent outcomes from being distorted by age-related factors. Those who do not have an ED and/or have a severe mental illness (e.g., severe major depression, anxiety with alcohol abuse disorder, or comorbid psychotic symptoms); a history of frequent or recent suicide attempts; or a high level of functional impairment will also be excluded. People with severe somatoform symptoms will not be excluded unless they have a high level of disability. People who have difficulty understanding the Spanish language; have an intellectual or legal disability; are already participating in a clinical trial; or are undergoing private therapy sessions will be excluded. Potential participants will be asked about previous pharmacological treatment at pre-treatment to control that variable.

### Interventions

#### Group brief transdiagnostic cognitive-behavioural therapy (group tCBT)

It was developed by Cano-Vindel [43] and is based on the Unified Protocol for the Transdiagnostic Treatment of Emotional Disorders (UP) [44] and the IAPT programme [21]. It consists of seven 90-min sessions over 12–16 weeks and is conducted by a non-assessor clinical psychologist (hereafter the therapist), with 8–10 participants per group. Sessions are weekly or biweekly, and reduce in frequency as the intervention progresses; they are described below. (See Table 1 for the timeline.) The activities and homework are supported with materials such as theory documents, a CD for progressive muscle relaxation, self-recording sheets, and a therapy web. For more information, see González-Blanch et al. [43].

**Table 1 Tab1:** Group tCBT’s session timeline [43]

Therapy contents	Sessions						
	1	2	3	4	5	6	7
1. Psychoeducation	**×**	**×**					
2. Relaxation	**×**	**×**					
3. Cognitive restructuring			**×**	**×**	**×**	**×**	**×**
4. Behavioural techniques				**×**	**×**	**×**	**×**
5. Relapse prevention							**×**

##### Session 1: introduction and psychoeducation (I)

The main objective of this session is to inform participants about the psychosocial nature of EDs and encourage them to play an active role in the treatment so that they attend all sessions and complete the assigned homework.

The first session begins with a presentation by the psychologist, who explains the protocol. The participants introduce themselves and talk about their symptoms and therapy expectations. They are informed about the group treatment: general objectives, components, functioning, timeline, and therapy rules (i.e., punctuality, confidentiality, respect, and notification if they are not going to attend), and provided with information about the treatment web [45] and its use. The psychoeducation then begins. They are given information about emotions, their adaptive role, and when they start to be maladaptive and become EDs. Participants are told how to manage stress and emotions cognitively, physiologically, and behaviourally, and how people sometimes magnify stimuli perceived as threatening or spend too much time thinking about a problem. (Both interpretational and attentional biases are therapy targets.) All this may be explained using personal examples drawn from the group members. Next, they are taught a diaphragmatic breathing technique, an emotion regulation tool to reduce psychophysiological activation. Finally, homework is given: participants are asked to read the therapy documents and online resources and practise the breathing technique with self-recording. The therapist gives homework to participants after each session and emphasizes the importance of completing it daily and putting the acquired knowledge into practice.

##### Session 2: psychoeducation (II) and relaxation

The objective of this session is to talk about the nervous system and the links between stress, coping, emotions, and health, as well as how to reduce psychophysiological activation through emotional self-regulation strategies.

This and the following sessions begin with a summary of the previous one and a review of the homework. The therapist discusses stress (i.e., definitions, theoretical models, phases, psychosomatic symptoms, and coping), the link between cognition and emotion, and presents strategies designed to downregulate the magnification and attention biases referred to in Session 1. Next, the diaphragmatic breathing technique is reviewed and practised, and progressive muscle relaxation is introduced as a useful emotional self-regulation strategy. The homework is given at the end: daily practice and self-recording of both diaphragmatic breathing and progressive muscle relaxation and the reading of an introductory document on cognitive therapy.

##### Session 3: cognitive restructuring (I)

The objective of this session is to introduce more emotional self-regulation strategies and teach participants to identify maladaptive thinking styles that generate and/or maintain emotional distress.

After the previous session summary and the review of the homework, participants talk about the usefulness of pleasurable activities and physical exercise. Then, the concept of irrational thinking (and how emotions can influence it) is introduced, and the integrative cognitive restructuring model [46] is explained. It consists of 3 phases: (1) information provided by the therapist regarding the problem (e.g., emotions, cognitions distorted, physiological responses, consequences, and emotional dysregulation problems); (2) self-observation, which implies the learning of complex cognitive concepts (e.g., cognitive biases, metacognition, and dysfunctional schemas), self-perception, and the recording thereof; and (3) cognitive restructuring, that is, training on the analysis and reassessment of threats, attention focus, problem-solving skills and how to improve self-efficacy and self-esteem. Some theoretical models are introduced for motivational purposes: the expectancy model and self-fulfilling prophecy (to illustrate cognition-behaviour interaction) [47] and the theory of attribution [48]. Finally, homework: the practice and self-recording of both relaxation techniques, pleasurable activities, physical exercise, self-observation (i.e., event, situation, cognition, physiological response, emotion, behaviour, and consequences), and the reading of a document on thinking distortions and cognitive biases.

##### Session 4: cognitive restructuring (II)

The objective of this session is to learn how to modify maladaptive thoughts through cognitive restructuring and positive self-instruction and to plan a behavioural experiment.

In this session, cognitive restructuring is practised using the homework self-observations, with an especial focus on the principal interpretational biases. Participants must (1) identify the cognitive processes that generate emotional distress; (2) identify the cognitive mistakes; and (3) turn them into more adaptive and rational thoughts. To encourage the latter, the positive self-instruction model [49] is introduced. The practice and self-recording of relaxation techniques, pleasurable activities, physical exercise, and cognitive restructuring are again given for homework; participants are also asked to design a personalized behavioural experiment to confront and disconfirm their irrational thoughts.

##### Sessions 5 and 6: cognitive restructuring (III) and problem-solving

These sessions continue with cognitive restructuring with positive self-instruction but behavioural training is now added. The therapist stresses the need to face stimuli that generate distress following successive approximation and reinforcement. This approach, coupled with cognitive restructuring, allows participants to disconfirm irrational beliefs and the anticipated negative consequences that encourage avoidance. The sessions also include several psychological techniques that are taught in the consultation for home practice: self-observation, stimulus control, reinforced behavioural training, exposure without security behaviours, and coping skills. A problem-solving technique [50] is introduced using an example from the group. These sessions are also used to reinforce group achievements and correct mistakes. The homework includes the practice and recording of all techniques learnt so far (i.e., diaphragmatic breathing, progressive muscle relaxation, pleasurable activities, physical exercise, cognitive restructuring, and behavioural experiments).

##### Session 7: relapse prevention and closing

The objective of this session is to review and reinforce the emotional self-regulation and cognitive-behavioural strategies learnt during the intervention. Finally, relapses are discussed not in terms of failure but challenges that have to be worked on, and the various techniques that have been learnt are generalized to other events and situations that may arise in the future.

#### Individual brief transdiagnostic cognitive-behavioural therapy (individual tCBT)

This is an adaption of the group therapy, with the same phases and the same order. However, since it is an individual intervention, its duration and the associated exercises can be personalized. It consists of a minimum of 6 and a maximum of 8 sessions of 30–60 min and is provided by a clinical psychologist not involved in the assessments.

#### Treatment as usual (TAU)

Participants in this group will be provided with common primary care treatment by a GP in a face-to-face consultation that seldom lasts more than 10 min. TAU usually consists of pharmacological treatment, though it might also involve practical advice or even no treatment at all [51]. The first consultation will count as part of the recruitment process and, if the patient agrees to participate in the trial, no therapy will be provided until they are allocated to a group. Once in the TAU intervention, if the practitioner recommends psychological treatment (e.g., referral to specialized care), the participant would be excluded to avoid contamination between clusters. TAU does not comprise a specific number of sessions; it will end when the GP considers the patient recovered.

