### Recruitment

Participants will be recruited from primary care by their GPs. All patients aged 18–65 who are considered to meet eligibility criteria (based on their previous history of ED, diagnostic criteria, or clinician suspicion) will be encouraged to participate. After signing an informed consent form, the participant will have an appointment with an assessor psychologist, who will administer the measurement tools. If the participant does not meet the criteria, they will be referred back to their GP. If the participant is excluded due to a severe mental illness or a high-level disability, the GP will be advised to refer them to specialized care. Patients will receive no economic compensation for their participation in the trial.

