#### Collection process

First, the 4-item PHQ ultra-brief subscale (PHQ-4) [91] will be used for the recruitment phase. The PHQ-4 gathers 2 items from the PHQ-2 and 2 from the GAD-2 (short versions of the PHQ-9 and GAD-7, respectively). It has been used in a Spanish primary care population (Spearman-Brown’s *ρ*_PHQ-4_ = .72; *ρ*_PHQ-2_ = .86; *ρ*_GAD-2_ = .76) [92]. A score greater than or equal to 3 would indicate the need for additional assessment (PHQ-2: a sensitivity of 90% and a specificity of 61%; GAD-2: a sensitivity of 88% and a specificity of 61%). It can be an extremely useful tool, as it helps to accelerate the screening process. It has been suggested, however, that both PHQ-2 and GAD-2 sum scores should be regarded separately in primary care samples [92]. The first item from the PHQ-PD has been added to screen panic disorder.

Second, depression, anxiety, panic, and somatizations will be assessed through the PHQ subscales mentioned above. If a participant scores as having a severe ED (depressive or anxiety disorder) or a non-emotional mental illness, or if the diagnosis is not clear, they will undergo a second evaluation with a gold-standard tool. The Structured Clinical Interview for DSM Axis-I Disorders (SCID-I) [93] will be used to assess panic and depression disorders and the Composite International Diagnostic Interview (CIDI) [94] will be used for GAD (since the former may not be adequate as it only includes one item for GAD). If these tools confirm the PHQ results, the patient will be referred to their GP, who will refer them to specialized care. The same will apply to those who score high in the SDS. All measures, except the PHQ-4, the SCID-I, the CIDI, and the treatment satisfaction question, will be collected at baseline, immediately after treatment, and 6 and 12 months later (see Table 2). Data will be also collected from medical records for the 3 months before participation in the study. To facilitate completion, the questionnaires may be answered in person, by email, online, or by phone.

To reduce the number of withdrawals, the clinical psychologists will telephone the participants to encourage them to continue with the treatment and/or to participate in the follow-up assessments. People who drop out of the intervention will still be invited to complete the questionnaires, especially at the first post-treatment assessment (immediately after the intervention).

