### Statistical methods

#### Analysis of clinical effectiveness

Data analysis will be carried out using SPSS Statistics. Effectiveness-related data will be analysed using intention-to-treat and per-protocol approaches. After the homogeneity of intra- and inter-groups is checked, changes over time (baseline, post-intervention, and follow-ups) in primary and secondary outcomes will be analysed using linear mixed models (LMMs), since this method has been recommended rather than ANOVA or MANOVA analyses because LMMs do not require participants with missing values to be omitted nor imputed, and they are more adequate for repeated measures [95]. Likewise, effect sizes (Cohen’s *d* with bias corrections) will be calculated, as well as their accuracy (by taking into account the number of treatment sessions). The percentage of patients in each cluster who experience a 50% decrease in the number of clinical symptoms and scores to one standard deviation and the percentage of cases with a probable ED before and after receiving treatment (according to cut-off criteria) will be calculated. Therapeutic success criteria will be determined by obtaining post-intervention means significantly lower (*p* ≤ .05) and medium/large effect sizes significantly higher than those of the controls, especially in the ED scores. Clusters will be also compared regarding impairment, quality of life, emotion regulation biases, and satisfaction with treatment.

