#### Cost analysis

Cost-related data will be collected through medical records and ad hoc questionnaires, from 3 months before inclusion in the study to 12 months after the intervention. Direct costs will be calculated by adding the ED-related costs due to medication use (antidepressants, anxiolytics, hypnotics, and sedatives), medical tests and other health services, and health personnel (primary/specialized care and public/private care). Medication costs will be calculated by multiplying price per milligram (€/mg) according to the Vademecum International (including VAT) [96] by the daily dose (mg) and the number of days of drug treatment. Cost data relating to medical tests and the use of health services will be obtained through the fee information published on the Andalusian Health Service’s official website [97]. Since a group psychotherapy session does not have a specific tariff, it will be considered as a GP consultation without medical tests because GPs and clinical psychologists have similar basic salaries [98]. Indirect costs will be calculated by multiplying the days of ED-related sick leave by the participant’s current daily minimum salary; the expense of replacement workers will also be factored in when incurred. Total costs will be obtained by summing direct and indirect costs.

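### TAU participants are excluded after randomisation once the GP recommends psychological treatment, with no counterpart in the tCBT arms; this conflicts with the planned intention-to-treat and cost analyses

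*Protocol article*

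**What the plan says.** Four parts of the protocol article bear on this point.

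- **Treatment as usual (TAU).** The rule begins "Once in the TAU intervention", so it applies after allocation. It reads: "if the practitioner recommends psychological treatment (e.g., referral to specialized care), the participant would be excluded to avoid contamination between clusters". The only reason given is contamination. The trigger is the GP's recommendation, not receipt of therapy.
- **Group tCBT and individual tCBT.** Neither section has a corresponding rule for a participant who is advised to seek, or obtains, psychological care outside the trial. The Eligibility criteria section bars people already in private therapy, but as an entry criterion.
- **Analysis of clinical effectiveness.** "Effectiveness-related data will be analysed using intention-to-treat and per-protocol approaches". The section does not say which set contains the excluded TAU participants.
- **Cost analysis.** Direct costs include "health personnel (primary/specialized care and public/private care", and costs are gathered up to 12 months after the intervention.

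The Collection process section provides for continued assessment of one group: "People who drop out of the intervention will still be invited to complete the questionnaires". It does not mention people whom the protocol itself excludes.

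**The concern.** Intention-to-treat means that every randomised participant is analysed in the arm to which they were allocated, whatever happens next. A rule that removes people from one arm because of a later event breaks that. The groups compared are then no longer the groups that randomisation made comparable.

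Two of the trial's hypotheses depend directly on the TAU arm: "The TAU will be the least effective" and "The TAU will have the least cost-effectiveness and cost-utility ratios". Hypothesis 5 carries the same comparisons to 6 and 12 months. If the people removed differ in prognosis from those who remain, the clinical contrasts are biased. The incremental cost-effectiveness and cost-utility ratios, which are the stated aim of the trial, also lose these participants' later costs and QALYs.

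**Working it through.** **1. The passages side by side.** The TAU rule acts after allocation, in one of three arms, on a post-baseline event. The effectiveness section promises intention-to-treat. The only text on continued assessment covers people who stop the intervention, not people whom the protocol excludes. The Eligibility criteria section uses the same word, excluded, for people who never enter the trial. No text gives it a milder meaning here.

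**2. Does the contamination reason cover the rule?** Only in part. The Background section says that waits for specialised care are too long, so a participant can be removed on a recommendation without having had any therapy. The Blinding section intends GPs to be unaware of allocation, so a GP could recommend therapy to a tCBT participant too, and that participant would stay in.

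**3. Is the exclusion related to outcome?** Plausibly. The TAU section names two ways out of TAU: the GP judges the patient recovered, or the patient is excluded on a recommendation. At screening, the protocol links referral to the specialised level with severity: "If the participant is excluded due to a severe mental illness or a high-level disability, the GP will be advised to refer them to specialized" (quote cut before its last word). That text concerns people who are not enrolled, so it makes the link plausible but does not establish it for randomised mild-to-moderate cases.

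**4. The plan's own figures.** A one-way ANOVA with 3 groups, f = 0.3 and alpha = .05 first reaches 80% power at N = 111 (power 0.803), or 37 per arm. 111 × 1.15 = 127.65, rounded up to 128, or 128/3 = 42.7 per arm. Both stated figures reproduce. The allowance for losses is 42.7 − 37 = 5.7 per arm.

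**5. Size, as an illustration.** The documents give neither a referral rate nor the outcome of referred patients, so both are assumed. Let p be the share of TAU referred and δ how much worse they would score than the rest of TAU, in SD.

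Full TAU mean = m + p × δ; after exclusion it is m; shift = p × δ.

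| p | δ = 0 | δ = 0.5 | δ = 1.0 | Excluded, of 42.7 |
|---|---|---|---|---|
| 5% | 0 | 0.025 (4% of 0.6) | 0.05 (8%) | 2.1 |
| 10% | 0 | 0.05 (8%) | 0.10 (17%) | 4.3 |
| 20% | 0 | 0.10 (17%) | 0.20 (33%) | 8.5 |

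At 20% the exclusions alone exceed the allowance of 5.7. The Sample size section does not say whether such exclusions count within it.

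**6. Cross-check with a second model.** Remove the top share q of TAU by referral propensity, which has correlation ρ with outcome. The shift is ρ × φ(z)/(1 − q), where z is the normal quantile at 1 − q. Pairwise power is Φ(d/se − 1.96), with se = √(1/37 + v/(37(1 − q))) and v the variance left in TAU. With nobody removed, d = 0.60 and power is 0.73. With ρ = 0.5:

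| q | Shift (SD) | Observed difference (SD) | Power | Implied δ = shift/q |
|---|---|---|---|---|
| 5% | 0.054 | 0.546 | 0.65 | 1.1 |
| 10% | 0.097 | 0.503 | 0.57 | 0.97 |
| 20% | 0.175 | 0.425 | 0.43 | 0.88 |

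This agrees with the δ = 1.0 column above. With ρ = 0 there is no bias, only a smaller arm.

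**The case against.** **The excluded need not be TAU's worst or costliest cases.** A reader might infer that the rule removes people for doing badly. The documents do not say so. Contamination is the only reason given, and the link between referral and severity is stated only for screening. The Background section notes that patients tend to prefer psychological treatment, so a GP may recommend it for that reason. This objection stands: selection on outcome is plausible but not shown.

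**The direction could reverse.** If these participants were followed and the psychological care they then received helped them, δ would be negative. Excluding them would then make TAU look worse and favour tCBT. This stands too. The tables cover only δ of zero or more. It is equally unsupported to infer that the rule inflates the tCBT effect.

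**Excluded may mean only leaving the TAU intervention.** A reader might infer either this or that the data will certainly be thrown away. The protocol settles neither. The mild reading would be harmless, but it is written nowhere, and the invitation to people who drop out does not clearly reach people removed by rule.

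**Mixed models tolerate missing values.** They do, and they would use data up to exclusion. That removes bias only if the missingness is explained by what was observed, and it does not recover costs and QALYs that were never collected.

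**Contamination means something different in the tCBT arms.** Those arms already receive psychological treatment, so the authors' reason does not transfer directly. That explains the asymmetry, but it does not restore a randomised comparison.

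**Conclusion.** The concern holds. As written, the TAU rule removes randomised participants from one arm on a post-allocation event, with no statement that they remain in assessment or analysis. That is incompatible with the promised intention-to-treat analysis, and it drops specialised-care costs that the cost analysis sets out to include. This part rests on the text alone.

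The bias is a matter of inference. If referred patients are those not improving, the remaining TAU arm looks healthier and cheaper, which works against Hypotheses 2 and 4. Neither the direction nor the size is established. Under assumed referral of 5-20% and outcomes 0-1.0 SD worse, the TAU mean shifts by 0-0.20 SD, which is 0-33% of d = 0.6. No figure in the Sample size section is put in doubt by this point.

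It needs settling in the protocol rather than at analysis, because assessments not made after exclusion cannot be recovered.

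**What to change.** Reconcile the Treatment as usual section with the Analysis of clinical effectiveness section by replacing the exclusion with wording to this effect:

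- A TAU participant whose GP recommends psychological treatment stays in the trial and is assessed at every planned time point.
- The participant is analysed in the TAU arm in the intention-to-treat effectiveness analysis and in the economic analyses, with all costs counted.
- The date and type of any psychological care are recorded.
- Removal of such participants is limited to the per-protocol analysis.
- Psychological care obtained outside the trial by tCBT participants is recorded and handled in the same way.

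Nothing changes in how GPs treat or refer. The cost is a short protocol change and a few more questionnaires from people already enrolled. The price in interpretation is that the TAU estimate then includes the effect of referral, so it describes usual care with its referrals rather than usual care without psychological treatment. The per-protocol analysis can still address the latter.
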